#### 2.4.4. Cost-Effectiveness of the Program

To assess the cost-effectiveness of the intervention [38], we will use a cost-effectiveness ratio (CER), which quantifies the relationship between the total cost of the intervention and the improvement in the primary outcomes. In addition, the CER of improvement in QoL and functionality will be determined using the following formula:$$CER=\frac{TC}{\Delta E}$$
where

TC = Total cost of the program (NW or Fit 5-Fitness Cards);ΔE = Change in average outcomes scores (post-intervention minus pre-intervention).

The incremental cost-effectiveness ratio (ICER) will be computed to compare the economic and functional impact of NW against the Fit 5-Fitness Cards program. The ICER will be determined using the following equation [39]:$$ICER=\frac{C1-C0}{E1-E0}$$
where

C1 = Total cost of the NW intervention;C0 = Total cost of the Fit 5-Fitness Cards program;E1 = Post-intervention outcome for the NW group (e.g., average QoL score);E0 = Post-intervention outcome for the Fit 5-Fitness Cards group.

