#### 2.4.2. Functionality

Dynamic Balance and Gait Speed: The “Timed Up and Go Test” (TUGT) will be employed, a reliable assessment tool for individuals with ID [31]. In a sample of 31 adults with ID, the TUG proved to be a feasible assessment tool, demonstrating excellent test–retest reliability (ICC: 0.90; 95% CI: 0.82–0.95) [32];Flexibility: The sit and reach test (SR) will be used to assess the impact of the program on the participants’ lower-body flexibility. For performing the SR, the participants will sit on the floor without shoes and with knees straight, and feet placed flat against the front-end panel of a standard SR box. Then, they will be asked to slowly reach forward as far as possible while placing the palms down along the measuring scale placed on the top of the box and to hold the position for approximately 2 s. The most distant point reached with the fingertips will be recorded (to the nearest centimeter). The best of two trials will be retained for analysis. The SR has demonstrated high reliability in a sample of 63 adolescents with ID (ICC = 0.97) [33] and has been previously used to assess fitness levels in adults with ID [34];Cardiorespiratory Fitness: Heart rate (HR) data will be collected using a Polar HR monitor (Polar Team Pro for iPad, version 1.0.1) during the tests. This method has been previously applied to individuals with ID [3].

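### The cost-effectiveness ratios set programme totals against per-person means and score a faster Timed Up and Go as a loss, and the two ratios use different effect measures

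*Protocol article*

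**What the plan says.** Section 2.4.4 writes out two formulas and defines each term.

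- **Single-programme ratio:** CER = TC/ΔE. TC is "Total cost of the program (NW or Fit 5-Fitness Cards") and ΔE is "Change in average outcomes scores (post-intervention minus pre-intervention"). The section gives the purpose as quantifying "the relationship between the total cost of the intervention and the improvement in the primary outcomes", and adds that "the CER of improvement in QoL and functionality will be determined using the following formula".
- **Incremental ratio:** ICER = (C1 − C0)/(E1 − E0). C1 and C0 are again the total costs of the two programmes. E1 is "Post-intervention outcome for the NW group (e.g., average QoL score"), and E0 is the matching post-intervention outcome for Fit 5-Fitness Cards.

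Under functionality, section 2.4.2 states: "The “Timed Up and Go Test” (TUGT) will be employed". The section gives no per-participant cost basis, no rule for outcomes where a lower value is better, and no reason why one ratio uses change and the other uses post scores.

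Section 2.1 describes a cluster-randomised crossover in which each group takes both programmes. Section 2.2 plans 100 participants (67 required) in four centres. Section 2.3 randomises the centres without stratification or pairing.

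**The concern.** These are stated definitions, so the question is what they produce when followed.

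1. **Units.** A programme total in the numerator meets a per-person mean in the denominator. The result depends on how many people were treated.
2. **Sign.** Post minus pre is applied to every outcome. The Timed Up and Go is a time, so a fall is an improvement. The article does not say this, but it follows from a timed task. The formula then contradicts the section's own purpose of relating cost to improvement.
3. **Effect measure.** The CER uses change and the ICER uses raw post scores for two groups, although each participant is due to receive both programmes.

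The abstract says cost-effectiveness will be evaluated, and the discussion offers physical activity to policymakers as a cost-effective strategy. Functionality is part of the primary objective, so the Timed Up and Go is not a marginal outcome. A ratio that changes with enrolment or carries the wrong sign cannot serve that use.

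**Working it through.** The article gives no costs, effects or ratios, so there is no stated figure to reproduce. Every cost and effect below is an assumption. Only the sizes 67 and 100 come from the article (section 2.2).

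**1. Scale.** Assume 150 per person for NW, 100 for Fit 5, and mean quality-of-life gains of 4 and 2 points.

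| | N = 67 | N = 100 | Per person, any N |
|---|---|---|---|
| NW CER | 150 × 67/4 = 2,512.5 | 150 × 100/4 = 3,750 | 150/4 = 37.5 |
| ICER | 50 × 67/2 = 1,675 | 50 × 100/2 = 2,500 | 50/2 = 25 |

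As written, each ratio is N times the per-person ratio.

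If the numbers treated differ, the ICER is no longer a simple multiple. With 95 on one programme and 80 on the other, 100 per person on both, and an effect difference of 2 points, it is (9,500 − 8,000)/2 = 750. The incremental cost per person is 0, so the per-person ICER is 0.

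**2. Sign (per-person costs, to isolate this fault).**

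- CER, 10 s to 9 s (better): 150/(9 − 10) = −150.
- CER, 10 s to 11 s (worse): 150/(11 − 10) = +150.
- ICER, NW 8.5 s against Fit 5 9.0 s, NW dearer by 50: 50/(8.5 − 9.0) = −100. Scored as improvement it is 50/(9.0 − 8.5) = +100.

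With NW the dearer programme, −100 would normally be read as dearer and worse. In this example NW is dearer and better.

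**3. Post scores against change.** Group A takes NW first and Group B takes Fit 5 first. Assume gains of 4 (NW) and 2 (Fit 5), so the true difference is 2 and the per-person ICER is 50/2 = 25. Let Group A start at 103 and Group B at 100.

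- *Both periods, equal sequences, period effect of 1, no carryover.* Post-NW means are 107 (A) and 105 (B), average 106. Post-Fit 5 means are 106 (A) and 102 (B), average 104. The difference is 2.00. The change scores also give 4 − 2 = 2.00. Post scores do no harm here, despite the 3-point baseline gap.
- *Sequences 75:25, same period effect.* Post-NW: 0.75 × 107 + 0.25 × 105 = 106.5. Post-Fit 5: 0.75 × 106 + 0.25 × 102 = 105. The difference is 1.50 and the ICER 33.3. Change still gives 2.00 and 25. With 25:75 the post difference is 2.50 and the ICER 20.
- *Equal sequences, no period effect, 25% of the first gain persisting through the second period.* Post-NW: 107 and 104.5, average 105.75. Post-Fit 5: 106 and 102, average 104. The difference is 1.75 and the ICER 28.6, against 25 on change.
- *First period only.* 107 − 102 = 5, so the ICER is 10. With Group A starting at 97, 101 − 102 = −1 and the ICER is −50. Change gives 25 in both cases.

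With a smaller true difference of 1 point, the same ±3 gap in a first-period comparison gives a denominator of 1 + 3 = 4 (ICER shrunk fourfold) or 1 − 3 = −2 (sign reversed).

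Dropout between periods has a similar effect: the two post-score means no longer contain the same people, so the baseline gap stops cancelling.

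**The case against.** **Total cost may mean all cost components per participant.** The scale fault would then vanish, and detailed costing is often left to a fuller document. But section 2.4.4 speaks of the cost of the program or intervention and nowhere of a cost per person, so the plain reading is a programme total. On that reading, if both programmes treat the same cohort, N is common. The ranking of the two CERs and the sign of the ICER then survive, and the fault is one of units. That stands, but only while the numbers treated are equal. Section 2.2 raises 67 to 100 for dropout, so equality is not assured.

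**The sign problem is narrow and visible.** Quality of life is the ICER's only example, and the sit and reach test is scored as distance reached, so neither is affected. A negative Timed Up and Go ratio keeps its absolute size. This limits the reach of the fault. It does not remove the conflict with the stated purpose.

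**Post scores are not an error in themselves.** This stands. A reader might infer from the wording about an NW group and a Fit 5 group that the ICER will be driven by baseline differences between centres, or more broadly that all the ratios will be wrong. The article does not support either inference. Sections 2.1, 2.3 and 2.5 put every participant through both programmes, so the NW group can equally mean all post-NW measurements over both periods. In a complete, balanced crossover without carryover, post scores then give the same expected difference as change.

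**Cost-effectiveness is secondary.** It is absent from the listed primary and secondary objectives, the study calls itself a pilot, and no efficacy result depends on section 2.4.4. That limits the weight of the point, but the formulas still need correcting.

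**Conclusion.** The point holds in three parts of unequal strength.

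- **Units:** wrong as written on the plain reading of total cost. Both ratios are inflated by the number treated, 67 to 100 times at the planned sizes. Unequal numbers can create an incremental cost where none exists per person (750 against 0 in the example).
- **Sign:** wrong as written for the Timed Up and Go in both ratios, and for any other outcome where lower is better. The quality-of-life and sit and reach ratios are not affected.
- **Post against change:** an inconsistency that biases the ICER only if first-period groups alone are compared, or with carryover, dropout between periods, or unequal sequences combined with a period effect. These are plausible with four centres and unrestricted randomisation, but not certain. The fourfold and sign-reversed ICERs belong to the first-period comparison alone.

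All amounts rest on assumed costs and effects. The units and sign faults stand without the third. The section should be corrected before any ratio is calculated.

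**What to change.** Reword section 2.4.4:

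1. Use mean cost per participant in both formulas, and state which participants are counted.
2. Score every outcome so that a positive value means benefit. For the Timed Up and Go, use pre minus post. If a ratio is planned for heart rate, which section 2.4.2 also lists, state its direction.
3. Use one effect definition in both ratios. Take E1 − E0 as the within-participant NW minus Fit 5 difference over both periods, adjusted for period, and do not describe the programmes as two separate groups.

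This needs no new data or visits. Section 2.6 names no single within-participant model for this difference, so a sentence there or in the analysis plan should say which estimate supplies E1 − E0.

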#### 2.4.5. Post-Intervention Average Weekly Physical Activity

Before the intervention begins, the participants and their parents will be asked to write the main physical activities (modality and duration) that they usually perform together in a typical week. Once the intervention ends (7 months after the start of the exercise program), a physical activity log will be given to the participants and their parents. They will be asked to register any type of physical activity (modality and duration) performed during a typical week of each month for the following six months.

Four NW poles will be given to the participants (two) and their parents (two) who complete the whole intervention. They will be encouraged to continue practicing NW by themselves for the next six months. Additionally, the registered offices that took part in the research will allow the use of the facilities in which the Fit 5-Fitness Cards and NW program took place at least two days per week, so that the participants and their parents could keep performing Fit 5-Fitness Cards and NW activities, also for the next six months.

Health-related PF, feasibility and QoL measurements will be carried out one week before the start of the training programs (To), once a week after the completion of the first stage (T1), one month later (T2), at the end of the second phase (T3), and six months later (T4). Record logs will be returned at T0 and T4. All the field-based tests and the questionnaire will be administered by the people in charge of the exercise intervention performed in each ID registered office.

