## Abstract

Background: We aim to evaluate the effect of the Nordic Walking program on the quality of life and functionality of individuals with intellectual disabilities; Methods: The NORDIN-JOY study is designed as a multicenter, randomized crossover trial. Participants in the experimental group will engage in a Nordic Walking intervention, while those in the control group will participate in a Fit 5-Fitness Cards intervention. Both physical training programs will consist of two 60 min sessions per week over a three-month period. The study will assess measures of quality of life and physical fitness. Additionally, the feasibility and cost-effectiveness of both programs, as well as the average weekly physical activity levels during the six months following the intervention, will be evaluated; Results: The results of this study are anticipated to provide valuable insights into the effects of structured exercise interventions on individuals with intellectual disabilities. These findings will be disseminated through peer-reviewed journals and academic conferences; Conclusions: This protocol seeks to establish evidence on the impact of exercise programs in individuals with intellectual disabilities. The findings have the potential to inform specific recommendations for healthcare professionals, caregivers, and policymakers, promoting physical activity as a cost-effective strategy for improving care and quality of life in this population.

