### 2.3. Procedures

The registered sites will be randomly assigned to two groups using a random number table generated in Excel. The randomization process will be unrestricted, with no stratification or pairing of sites. To minimize selection bias, allocation concealment will be ensured by having an independent researcher generate the randomization sequence and store it in a secure file. Following the recruitment of the participating sites and the completion of the training period for monitors/caregivers, the randomization table will be unblinded, and the sites will be allocated to one of two groups. Preferably, the monitors/caregivers will be occupational therapists, physiotherapists, or social workers with specialized training in adapted exercise.

Group A will initially implement the NW program, followed by the Fit 5-Fitness Cards program. Conversely, Group B will undertake the programs in the reverse order. The random sequence will be generated by [name], while [name] will be responsible for informing the registered sites of the exercise sequence their members are required to follow.

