### 2.6. Statistical Analysis

Data will be reported as medians and interquartile ranges for non-normally distributed variables (checked with the Kolmogorov-Smirnoff test) or as means and standard deviations for normally distributed variables. Qualitative variables will be reported as n (%). The intra-cluster correlation coefficient and the cluster-specific effects will also be calculated. Inter-group quantitative variables will be compared, including the primary outcome, with an unpaired, two-tailed t test or the Mann–Whitney U test, as applicable. For inter-group dichotomous data comparison, the two-tailed chi-square tests will be used, with the Yates correction or Fisher’s exact test as appropriate. For repeated measures analysis, the two-way analysis of variance with the Bonferroni correction or the Friedman test, as appropriate, will be used. Comparison will be adjusted by cluster effect. Subgroup analysis of the primary outcome will include sex, age, BMI (normal, overweight and obese), level of physical activity (Inactive, Active), and level of ID (mild, moderate, severe). Multivariate regression models will adjust for confounders such as sex, age, BMI, physical activity, and ID level. Multicollinearity will be checked using the Variance Inflation Factor (VIF), with VIF > 5 indicating high collinearity [42]. Sensitivity analyses will assess robustness. Statistical significance will be set at a two-tailed *p*-value of less than 0.05. All analyses will be conducted using SPSS v24.0 software (IBM Corp., Armonk, NY, USA).

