This is the first randomized crossover study designed to evaluate the effects of physical activity interventions on individuals with a confirmed diagnosis of ID stemming from neurodevelopmental disorders or autism spectrum disorders. The objective of this protocol is to generate robust and reliable evidence on the impact of structured exercise programs in this population. The findings have the potential to guide specific recommendations for healthcare professionals, caregivers, and policymakers, highlighting physical activity as a cost-effective strategy to enhance care and improve the QoL for individuals with ID. Nevertheless, certain limitations may arise. One potential challenge is ensuring adherence to the program, as participants may initially lack motivation to engage in exercise. To address this, we anticipate that both NW and the Fit 5-Fitness Cards will be enjoyable activities. Nevertheless, we acknowledge the possibility of a decline in adherence during the follow-up phase, as the NW program will be unsupervised. Another potential limitation concerns the assessment of QoL, as the questionnaire will be completed by caregivers or family members rather than the participants themselves. Furthermore, the subjective nature of this outcome could affect the strength of the findings. Lastly, it should be mentioned that physical activity levels will be monitored through self-reported data, a subjective method prone to recall bias, especially when assessing sedentary behavior [47].

The expected results will also set the basis for further research. In this regard, future studies should explore the long-term effects of NW on physical and mental health outcomes among adults with ID taking into account severity levels. In addition, longitudinal studies could assess whether sustained participation leads to lasting improvements in mobility, cardiovascular health, and psychological well-being. Finally, comparative studies could examine NW against other physical activities to determine its relative effectiveness in promoting fitness and QoL.

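### Baseline and follow-up physical activity are recorded with different scope, so any comparison of the two would be expected to lean upwards if families report faithfully

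*Protocol article*

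**What the plan says.** Section 2.4.5 of the Protocol article describes two records of physical activity.

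- **Before the intervention**, participants and parents are asked to "write the main physical activities (modality and duration) that they usually perform together in a typical week".
- **After the intervention**, "a physical activity log will be given to the participants and their parents", and they are asked to "register any type of physical activity (modality and duration) performed during a typical week of each month for the following six months".

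The same section adds: "Record logs will be returned at T0 and T4". The Abstract names the outcome by saying that "the average weekly physical activity levels during the six months following the intervention, will be evaluated".

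Section 2.6 lists "level of physical activity (Inactive, Active" among the subgroup factors and also has physical activity as a covariate. It does not say which record supplies either. The Discussion concedes that "physical activity levels will be monitored through self-reported data, a subjective method prone to recall bias", but does not mention that the definition changes between baseline and follow-up.

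**The concern.** The two questions measure the same construct with different scope. Two limits present at baseline are absent at follow-up: the restriction to main activities, and the restriction to activities shared by participant and parents. Activity done alone, with other people or at the association's premises falls outside the baseline question but, read literally, inside the follow-up one.

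If the follow-up average is set against baseline, part of any rise would come from the wording. The Results section says the research is meant to help participants take up an active lifestyle, and a rise of this kind would seem to confirm that. Analysis could not repair it, because activity that was not asked about at T0 cannot be recovered later.

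A second, conditional risk concerns section 2.6. If the T0 item also supplies the Inactive/Active class or the physical-activity covariate, participants who are active without their parents could be misclassified.

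**Working it through.** The documents give no figure for this outcome, so there is nothing to reproduce. The check compares the two definitions and then applies a simple identity.

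**1. Definitions side by side (section 2.4.5)**

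| Feature | Baseline | Follow-up |
|---|---|---|
| Which activities | main ones | any type |
| With whom | participant and parents jointly | no restriction stated |
| Detail | modality and duration | modality and duration |
| Reference period | a typical week | a typical week, in each of six months |
| Occasions | one | monthly |

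Detail and reference week agree. The first two rows do not, and in both the follow-up scope contains the baseline scope.

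**2. Artefact under unchanged behaviour**

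Let W be true weekly activity, the same at both times. Let j be the share done jointly with parents, m the share of that joint activity counted as main, and s = j × m.

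- Recorded at baseline: sW. Recorded at follow-up: W.
- Apparent relative change: W/(sW) − 1 = 1/s − 1. Apparent absolute change: (1 − s)W.

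All values of j, m and s below are assumptions.

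| j | m | s | 1/s − 1 |
|---|---|---|---|
| 1 | 1 | 1 | 0% |
| 0.9 | 1 | 0.9 | +11% |
| 0.75 | 1 | 0.75 | +33% |
| 0.75 | 0.8 | 0.6 | +67% |
| 0.5 | 0.8 | 0.4 | +150% |

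At s = 0.7 the result is 1/0.7 − 1 = +43%. As an illustration in minutes, take an assumed W of 150 min/week with 60 captured at baseline (s = 60/150 = 0.4). The apparent gain is 150 − 60 = 90 min/week with no change in behaviour.

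**3. Narrow reading of the follow-up question**

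If families take the follow-up log to mean joint activity as well, j drops out and the artefact is 1/m − 1. That gives 0% at m = 1, +11% at m = 0.9 and +25% at m = 0.8. The artefact is smaller, but it is zero only if families have no secondary joint activity.

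**4. Incomplete logging at follow-up**

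If the log captures only a share c of true activity, the apparent change is c/s − 1. With s = 0.7 and c = 0.8 this is 0.8/0.7 − 1 = +14%; with c = 0.7 it is 0%; with c = 0.6 it is 0.6/0.7 − 1 = −14%. The sign is therefore fixed only under faithful reporting.

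**5. Is there a comparison group?**

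Section 2.3 states "Group A will initially implement the NW program, followed by the Fit 5-Fitness Cards program", and Group B takes the reverse order. By follow-up both groups have had both programs. A comparison between the two sequences would largely cancel the artefact; a pre-post comparison would not.

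**The case against.** The strongest reply is that no change from baseline is ever defined. The section title and the Abstract both speak of levels after the intervention, and section 2.6 gives no pre-post contrast for this variable. If only those levels are described, no false increase is reported. This stands as a limit on the claim. Still, a baseline question placed in this outcome's own section, with records returned at T0 and T4, has little use for this outcome unless the two are compared.

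Four further replies carry some weight.

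- **Scope of the log.** The people filling it in are participants and parents together, and the rest of the section is about shared activity. The log may be meant to cover family activity only, with the wider wording referring to modality. The text does not settle this. The main-versus-any difference would remain, and the ambiguity is itself a reason to align the forms.
- **Recall against log.** One might infer that baseline is pure recall while follow-up is a diary. The article itself refers to logs being returned at T0, so that contrast is not secure and the point does not rest on it.
- **Inactive/Active.** One might infer that participants active without their parents will be classed as inactive. Section 2.6 does not name the source of the class, and the rule may sit in a fuller document, so this remains conditional.
- **Weight.** Activity after the intervention is in neither the primary nor the secondary objectives, and the trial calls itself a pilot. This limits the importance of the point but not its correctness.

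**Conclusion.** The mismatch in wording is plain in the current text, and nothing elsewhere in the article aligns the two questions. Taken literally, the follow-up definition contains the baseline one. A follow-up-to-baseline comparison would therefore be expected to be biased upwards if families report faithfully and do at least some activity that is secondary or without the parents.

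The size is unknown. The range of 0% to +150% rests entirely on assumed capture shares between 1 and 0.4, and under-recording in the log could reduce, cancel or reverse it.

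A reader might go further and conclude that a spurious increase is bound to appear in the results. The documents do not support that: the comparison is implied rather than specified, the scope of the log can be read more narrowly, and the completeness of logging is unknown. What holds is that the two records are not comparable as worded, that no untreated group would reveal the artefact, and that the acknowledged self-report and recall bias does not cover it. This is a modest point about an outcome outside the stated objectives, and it is cheap to correct before T0.

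**What to change.** Before T0, adopt one form for T0 and for each follow-up month. It should record any type of physical activity by the participant, with anyone, by modality and duration, over one typical week. An optional column can mark activity done with parents, if shared activity is of interest in its own right. State in section 2.4.5 whether follow-up levels will be compared with baseline. If the Inactive/Active class or the physical-activity covariate is to come from activity records, derive it from this form and say so in section 2.6.

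With the same scope at both times, s = 1 and the definitional artefact is zero when behaviour is unchanged. Self-report error remains, as the article already acknowledges.

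The cost is one revised form and a little more recording for families at baseline, about a week if it is kept as a running log. The change has to be made before baseline data are collected.

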## 2. Materials and Methods

### 2.1. Study Design

This is a pilot study employing a crossover, cluster-randomized design with repeated measures. This design allows for a within-subject comparison, reducing inter-individual variability and increasing statistical efficiency compared to parallel-group trials, where each subject receives only one treatment [27]. Participating centers will be randomized in a 1:1 ratio into two groups. Two sequential interventions (NW program and Fit 5-Fitness Cards) will be conducted, separated by a 4-week washout period to mitigate potential carryover effects [27]. Following the washout period, the interventions will be repeated in reverse order, adhering strictly to the established protocol. A comprehensive outline of the design and procedures is presented in Figure 1.

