### 2.5. Intervention

Before the intervention allocation is revealed, the monitors/caregivers will receive training on both interventions to ensure that the explanations and implementation are as consistent as possible across all centers.

Both exercise training programs would be performed at the rate of two 60 min sessions per week for three months. After the wash-out period (one month), the training programs will be performed in reverse order for another three months. A follow-up phase of six months is scheduled once the intervention has finished (7 months).

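### As worded, the visit schedule does not fit the stated washout: T2 may fall after the second programme has begun, and T1 and T3 follow training at different lags

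*Protocol article*

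**What the plan says.** Section 2.4.5 lists five assessments of fitness, feasibility and quality of life. T0 is "one week before the start of the training programs (To"). The next three are "once a week after the completion of the first stage (T1), one month later (T2), at the end of the second phase (T3"). T4 follows six months after that. The tests and the questionnaire are administered at each centre by the people who run the exercise there.

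The calendar these visits must fit is given elsewhere:

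- Section 2.1: the two interventions are "separated by a 4-week washout period to mitigate potential carryover effects".
- Section 2.5: "Both exercise training programs would be performed at the rate of two 60 min sessions per week for three months", and then "After the wash-out period (one month), the training programs will be performed in reverse order for another three months".
- Section 2.4.5 on the total: "Once the intervention ends (7 months after the start of the exercise program").

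Section 2.4.4 defines a cost-effectiveness ratio for each programme from the post-minus-pre change. It does not name the visits that supply the two values.

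**The concern.** In a two-period crossover, the visit between the periods has two natural uses. It is the pre-programme value for the second programme, and it is the only visit placed to show whether the first programme's effect has faded. Both uses need it to come before the second programme starts. Read in sequence, the schedule puts it about a week too late.

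The visits that close the two periods are also worded differently: T1 comes after about a week without training, T3 as training ends. A change measured over period 1 and a change measured over period 2 would then differ in length and in time since the last session, whichever programme was given. That is a period effect created by the calendar.

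**Working it through.** **Inputs.** Each programme lasts three months at two sessions a week, which is 12 to 13 weeks and 24 to 26 sessions (section 2.5). The washout is four weeks (section 2.1) or one month (section 2.5). T0 is one week before training. T1 is read as one week after phase 1; the printed wording, "once a week after the completion of the first stage (T1"), is garbled, so this is an assumption. T3 is taken at the end of phase 2, lag 0.

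**The plan's own total.** 3 + 1 + 3 = 7 months, which agrees with section 2.4.5. No week is left over between the end of the washout and the start of phase 2.

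**Placing the visits.** Let m be the weeks in a month (4, or 365.25/12/7 = 4.35) and w the washout in weeks (4 or 4.35), counting from the start of phase 1.

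- T1 = 3m + 1; phase 2 starts at 3m + w; T3 = 6m + w.
- Reading 1, T2 counted from T1: T2 = 4m + 1, which is m + 1 − w weeks after phase 2 starts.
- Reading 2, T2 counted from the end of phase 1: T2 = 4m, which is m − w weeks after phase 2 starts.
- Period-1 interval, T0 to T1: 3m + 2.
- Period-2 interval, T2 to T3: 2m + w − 1 (reading 1) or 2m + w (reading 2).

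| m | w | T2 after start of phase 2, reading 1 | Sessions held by then (×2) | T2 after start of phase 2, reading 2 | T0 to T1 | T2 to T3, reading 1 | T2 to T3, reading 2 |
|---|---|---|---|---|---|---|---|
| 4 | 4 | 1.00 | 2.0 | 0.00 | 14.0 | 11.0 | 12.0 |
| 4 | 4.35 | 0.65 | 1.3 | −0.35 | 14.0 | 11.35 | 12.35 |
| 4.35 | 4 | 1.35 | 2.7 | 0.35 | 15.0 | 11.7 | 12.7 |
| 4.35 | 4.35 | 1.00 | 2.0 | 0.00 | 15.0 | 12.0 | 13.0 |

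Under reading 1, T2 falls inside phase 2 in every row. Section 2.5.1 gives the first four NW sessions to learning the technique, so Group B would be tested during those, and Group A after its first Fit 5 sessions. Under reading 2, T2 is at the end of the washout within rounding. The lag after training is 1 week at T1 and 0 at T3 on both readings.

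**Effect on NW minus Fit 5.** Suppose the calendar adds a shift p to every period-2 change, and the within-person difference in change is averaged with no period term. Group A (NW first) then carries −p and Group B +p. With centres of equal size, a in Group A and b in Group B, the bias is p(b − a)/(a + b):

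- 2:2 gives 0.
- 3:1 gives −0.5p.
- 4:0 gives −1.0p.

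The signs reverse if the majority is in Group B. A period term removes the shift when both sequences occur. At 4:0, period and programme cannot be separated.

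The document gives no outcome standard deviation and no rate of detraining, so p has no value here.

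**The case against.** The strongest reply is that the sentence is garbled and has a harmless reading. The washout is called one month in section 2.5 and T2 is "one month later (T2"), so the authors may simply have meant the end of the washout. Section 2.1 refers the reader to Figure 1, which is not shown and may settle the timing. This stands as far as T2 goes. Against it, T4 in the same list is counted from the visit before it, which favours counting T2 from T1, though it does not decide the matter.

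A second reply is that a shift common to both sequences does no harm at the 1:1 ratio in section 2.1, which for four centres means 2:2. That is correct if the split is realised. Section 2.3, however, describes unrestricted randomisation without stratification or pairing, and this allows an uneven split. Nor does the cancellation surely cover T2 under reading 1, because the two groups would have begun different programmes by then.

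Third, section 2.6 is a condensed account. Its two-way analysis of variance could include period, so the absence of a named period term does not show that none will be fitted. Treating T2 as the phase-2 baseline is likewise an inference: the incremental ratio in section 2.4.4 uses post-intervention values, and only the per-programme ratio uses change.

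Finally, a reader might infer that a late T2 shrinks every period-2 change and conceals carryover. The document does not support a direction. Early learning could raise T2, but section 2.4.3 expects soreness and fatigue that ease after two or three sessions, and these could lower it. Nothing suggests that two sessions would move a 96-item caregiver questionnaire.

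**Conclusion.** The point holds in a limited form. Section 2.4.5 fixes a schedule that, read in sequence, conflicts with the washout in sections 2.1 and 2.5 by 0.65 to 1.35 weeks. On either reading it closes the two periods at different lags: 1 week against 0, with intervals of about 15 weeks against 12 to 13 in calendar months. This rests on reading T1 as one week after phase 1 and T3 as the last day of phase 2.

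Two stronger conclusions are tempting: that T2 certainly falls inside the second programme, and that the two periods cannot be compared. The first depends on one reading of an unclear sentence. The second ignores that a common shift disappears at 2:2 or with a period term. What remains is an avoidable artefact of unknown size and sign, and a calendar that four centres could each read differently. Severity is minor to moderate.

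**What to change.** Reconcile the three sections with one rule for both periods. Take T0 and T2 in the last week before the first session of the coming programme. Take T1 and T3 at the same fixed interval after the last session of the programme just finished, with a stated visit window. Leave programme and washout lengths as they are.

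With one week before and one week after, each period's change spans 1 + 3m + 1 weeks, which is 14 or 15 in both periods, and covers the whole programme. If T3 moves to a week after training, state whether the six months to T4 run from T3 or from the end of training, and complete T3 before the poles for independent practice are handed out.

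The cost is one sentence, a matching Figure 1 and the centres' calendar. The number of visits does not change.
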